### Study Interventions

#### Surgery

Surgery to the primary site will be carried out by TLM or TORS, while a standard open approach will be used for neck dissection. These can be carried out as a single or staged procedure. Surgery should take place within 4 weeks (maximum 6 weeks) of study registration.

##### Transoral Laser Microsurgery (TLM) and marginal biopsies

TLM will be conducted according to the principles outlined by Steiner and Ambrosch [26]. Tumours will be removed in several (at least two) planned pieces following trans-tumoural resection. It is mandatory that representative marginal biopsies are taken from the tumour bed in all cases of TLM to ensure complete surgical removal of the tumour. Re-resection is allowed when initial marginal biopsies are found to be positive for microscopic disease. If positive marginal biopsies are obtained on re-resection, the patient is withdrawn from the trial.

##### Transoral Robotic Surgery (TORS)

TORS involves *en bloc* removal of the tumour as per the principles outlined in the da Vinci Transoral Surgery Procedure Guide:

http://www.uphs.upenn.edu/pennorl/education/documents/daVinciTORSProcedureGuide.pdf. As tumours are typically removed *en bloc*, marginal biopsies are usually not required.

##### Neck Dissection

Patients with clinically node negative (cN0) disease will undergo a selective neck dissection involving clearance of at least nodal levels II and III. Patients with clinically node positive (cN+) disease will undergo clearance of lymph node levels II and III and any additional involved lymph node levels. Patients with neck disease involving adjacent structures will undergo a modified radical neck dissection. In the case of non-lateralised primary tumours, as an alternative to non-surgical treatment (see below), some centres may undertake a selective neck dissection of the contralateral cN0 neck.

#### Radiotherapy

Patients should start RT within 5 weeks and no later than 6 weeks from surgery, so that combined treatment (surgery and RT) is completed within 11 weeks to avoid poor LC and survival rates that result from protracted treatment [11]. Patients are managed as category 1 as per the Royal College of Radiologists Guidelines and RT should be completed within 6 weeks for patients having 60Gy in 30 fractions and within 5 weeks for those having 50Gy in 25 fractions [27].

The primary tumour should be categorised as lateralised or non-lateralised based on clinical and radiological assessments.Lateralised tumour: Tonsillar tumour confined to the tonsillar fossa or extending onto or into the adjacent base of tongue and/or soft palate by less than 1 cm.Non-lateralised tumour: Tonsillar tumour that involves the adjacent base of tongue and/or soft palate by more than 1 cm or a tumour that arises from a midline structure (base of tongue, soft palate, posterior pharyngeal wall).

Patients with lateralised tumours should undergo unilateral neck RT, regardless of the nodal stage of the ipsilateral neck. Patients with non-lateralised tumours should undergo bilateral neck RT, except in cases where they have undergone contralateral selective neck dissection and pN0 status is confirmed on that side (see above).

PATHOS uses a geometric approach to define target volumes. Pre-operative imaging, pan-endoscopy reports, operative findings and pathology information should be used to delineate target volumes. The Clinical Target Volume 1 (CTV1) includes the primary and nodal tumour beds with a margin (1–1.5 cm) and all pathologically involved nodal levels. Arms B1, C1, C2 receive 60Gy/30 fractions and Arm B2 receives 50Gy/25 fractions. The Clinical Target Volume 2 (CTV2) includes all at risk uninvolved nodal levels that require prophylactic RT. Arms B1, C1, C2 receive 54Gy/30 fractions and Arm B2 receives 50Gy/25fractions. Some centres may, *a priori* opt to boost high-risk sub-volume(s) for patients in Group C to 66Gy/30 fractions. Neck node levels for prophylactic RT should be outlined according to updated consensus guidelines and atlas [28]. A margin (3–5 mm) will be added to each CTV to produce the respective Planning Target Volume.

Dose constraints to the following organs at risk will be used for treatment plan optimisation: spinal cord, brainstem, parotid glands. Investigators are also encouraged to contour swallowing-related structures. These include the pharyngeal constrictor muscles (superior, middle and inferior), supraglottic/glottic larynx, cricopharyngeus, oesophageal inlet, cervical oesophagus and oral cavity and should be outlined according to the PATHOS atlas of swallowing structures, itself based on previously published guidelines [24, 29]. The swallowing structures will not be used for treatment plan optimisation but swallowing outcomes will be correlated to the dose received by these structures. All patients will be planned using Intensity Modulated Radiotherapy (IMRT).

#### Chemotherapy

The following regimens can be used: Cisplatin 100 mg/m^2^ administered intravenously in a three weekly-cycle on days 1 and 22 of the RT schedule or Cisplatin 40 mg/m^2^ weekly for a maximum of 6 weeks. Carboplatin may be used instead of Cisplatin from cycle 2 onwards if the patient develops complications (ototoxicity, impaired renal function) related to Cisplatin.

### Assessments and outcomes

Comprehensive assessment of swallowing function requires a multidimensional panel of measures that incorporates instrumental examination of swallowing along with clinician-rated and patient reported outcomes. A functional outcomes panel for assessing swallowing function has been developed for PATHOS (Table 3). The following assessments will be conducted prior to surgery, 4 weeks post surgery and at 4 weeks, 6, 12 and 24 months post treatment: (1) MD Anderson Dysphagia Inventory score (MDADI); (2) Water swallow test (WST); (3) Performance Status Scale-Head and Neck (PSS-HN); (4) Quality of Life questionnaires (EORTC QLQ-C30 and EORTC QLQ-H&N35). Patients will also undergo a videofluoroscopy (VF) assessment prior to surgery, at 4 weeks post surgery and at 12 months post treatment. CTCAE Toxicity (v4.03) will be assessed weekly during and at the end of RT and at 4 weeks, 6, 12 and 24 months.

**Table 3 Tab3:** Functional outcomes panel for multidimensional assessment of swallowing function

Study	Description	Domain	Endpoint
MDADI	MDADI is a patient reported swallowing outcome measure, specifically designed and psychometrically validated for the head and neck cancer population	Swallowing-related QOL	Total/Composite, Global, Subscale Scores (continuous scores: 20 to 100)
WST	100mls WST is a timed swallowing test.	Swallow performance	Swallow capacity (mls per swallow)
			Swallow volume (mls per swallow)
VF	VF is the gold standard radiographic measure of swallowing function. It allows quantification of more objective endpoints of swallowing function including pathophysiology, swallowing efficiency and airway protection.	Swallow physiology	MBSImpairment profile (MBSImp) (continuous scores: oral impairment 0 to 22; pharyngeal impairment 0 to 29) [33]
		Airway protection	Penetration-aspiration scale (PAS) (ordinal score: 1 to 8)
			Aspiration, yes/no (binary) [34]
		Pharyngeal dysphagia grade	Videofluoroscopic Swallow Grade-Head & Neck (VSG-HN) (ordinal grade: 0 to 4)
PSS-HN	PSS-HN is a 3-item scale designed to evaluate functional performance of head and neck cancer patients according to normalcy of diet, eating in public and understandability of speech	Functional performance status	Normalcy of diet subscale, public eating subscale, understandability of speech scores (ordinal: 0 to 100)
EORTC QLQ C30 H&N35	QOL questionnaires	Health related QOL	Raw scores from scales and single item measures are transformed to a standardised 0–100 final scale score.

#### Primary outcome measures

The primary outcome of the phase II study will be swallowing function, measured using the 19-item composite MDADI score at 12 months post-treatment. The primary outcome of the planned phase III study will be overall survival (OS).

#### Secondary outcome measures

These will include data from: (1) functional outcomes panel (Table 3); (2) acute and late toxicity using CTCAE version 4.03; (3) QOL using EORTC QLQ C30 and H35 questionnaires; (4) overall survival (OS); (5) disease free survival (DFS); (6) locoregional control (LC); (7) distant metastases

### Sample size calculation

#### Phase II

Data show that a 10-point difference in mean MDADI score can differentiate aspirators from non-aspirators, tube-dependent from oral eaters and clinically distinct diet levels [30]. For the study to have 80 % power to detect this difference (two sided 5 % alpha), a sample size of 148 patients is required (i.e*n* = 74 in both randomisations). Given a 20 % loss to follow up as shown in previous studies, 186 patients will need to be randomised [20]. Assuming that 15 % of patients recruited are not randomised post-operatively (10 % who do not require adjuvant treatment and 5 % who decline randomisation) and that 10 % who are consented to the study will not be HPV positive at central HPV testing, we estimate that 242 patients will need to be enrolled into the phase II study.

#### Phase III

If the trial proceeds to phase III, then a sample size calculation for non-inferiority will be made. It is likely that around 800 patients will need to be recruited to prove that survival is maintained with de-intensified adjuvant therapy and European collaboration (through the EORTC) will be required for this.

### Statistical analyses

Mean MDADI scores at 12 months will be compared between arms using either a t-test or nonparametric methods depending upon distributions. We will adjust for the randomisation stratification variables using regression techniques. This primary analysis will be conducted when the last patient has had their 12 month assessment. An Independent Data Monitoring Committee will review the accumulating data (survival, toxicities, recruitment) at 6 monthly intervals. Strict monitoring has been built in for recurrence. A formal interim analysis will be performed after 38 patients have been randomised in each randomisation (19 per arm), treated and followed up for 6 months. Within each randomisation, a stopping rule will be based on observing an absolute observed difference of 6 or more locoregional recurrences and/or deaths in either of the intervention arms. For swallowing endpoints, subgroup analysis by T stage and tumour subsite (tonsil, soft palate, tongue base) will be carried out, as the most likely relevant clinical co-variables affecting swallowing function*.*

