### Method of randomisation

Patients in Groups B and C will be randomised to a trial arm using the method of minimisation with a random element. Randomisation will be performed centrally by the Wales Cancer Trials Unit (WCTU). Participants will be stratified prior to randomisation by T stage, N stage, smoking history and treating centre.

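### The primary comparison uses only the 12-month MDADI score despite an expected 20% loss; a repeated-measures model with pre-surgery MDADI would make better use of data already collected

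*Protocol article*

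**What the plan says.** Primary outcome measures defines the phase II endpoint as swallowing function "measured using the 19-item composite MDADI score at 12 months post-treatment".

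Statistical analyses names the comparison: "Mean MDADI scores at 12 months will be compared between arms", by a t-test or a nonparametric method according to how the scores are distributed. It continues: "We will adjust for the randomisation stratification variables using regression techniques". Method of randomisation identifies those variables: "Participants will be stratified prior to randomisation by T stage, N stage, smoking history and treating centre". No MDADI score is among them.

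Assessments and outcomes schedules MDADI at six visits: "prior to surgery, 4 weeks post surgery and at 4 weeks, 6, 12 and 24 months post treatment". Secondary outcome measures includes the functional outcomes panel, of which MDADI is part, so scores at other visits do have a secondary use.

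Sample size calculation, Phase II, allows for 20% "loss to follow up as shown in previous studies" by raising 148 evaluable patients to 186 randomised.

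**The concern.** A two-sample test on 12-month scores can use only patients who have one. Regression on T stage, N stage, smoking history and centre does not change that. The method as stated has two weaknesses.

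- **Efficiency.** Pre-surgery MDADI probably predicts 12-month MDADI, and a patient lost after 6 months has already supplied post-treatment scores. Neither enters the primary comparison.
- **Robustness.** A larger sample restores precision but does nothing about informative loss. If one arm loses more of its poor swallowers, the mean of those who remain in that arm is flattered.

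Deaths or recurrences in the de-intensified arms could produce such loss, and so could toxicity in the control arms. The result matters because a successful phase II leads to phase III.

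**Working it through.** **1. The plan's own figure.** 74 evaluable per randomisation / (1 − 0.20) = 92.5, rounded up to 93; 2 × 93 = 186. The stated figure reproduces.

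**2. Power at the planned loss.** The article gives no standard deviation, so I back-solve it. With 74 per randomisation and equal arms (the interim analysis has 19 per arm out of 38), there are 37 per arm. SD = 10 × √(37/2) / (1.960 + 0.842) = 15.35 by the normal approximation. With 93 randomised there are 46.5 per arm, and at 20% loss 46.5 × 0.80 = 37.2 complete cases per arm. Power for 10 points is 80.2%. With no loss it would be 88%. The loss is properly budgeted for power.

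**3. What the unused scores could add (assumed correlations).**

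*Earlier post-treatment scores.* Let f be the share of patients lost at 12 months who have an earlier score, and ρ the within-patient correlation. Approximate effective size per arm = 46.5 × (0.80 + 0.20 × f × ρ²).

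| f | ρ | Effective n per arm | Power |
|---|---|---|---|
| 0.5 | 0.4 | 37.9 | 81% |
| 0.5 | 0.8 | 40.2 | 83% |
| 1.0 | 0.4 | 38.7 | 82% |
| 1.0 | 0.8 | 43.2 | 86% |

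*Pre-surgery score as covariate, 37.2 complete cases per arm.* The residual SD is 15.35 × √(1 − r²). For r = 0.3, power is about 84%; for r = 0.5, about 90%.

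The two gains are calculated separately and should not be added.

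**4. Bias from unequal loss, no true difference.** If missing patients would have scored D points worse than those observed, an arm's observed mean exceeds its full mean by (proportion missing) × D. The bias in the difference is therefore (difference in proportion missing) × D.

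| Missing in the two arms | D = 15 | D = 30 |
|---|---|---|
| 15% v 25% | 0.10 × 15 = 1.5 | 0.10 × 30 = 3.0 |
| 10% v 30% | 0.20 × 15 = 3.0 | 0.20 × 30 = 6.0 |

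In simulation (46 randomised per arm, SD 15.35, 5,000 runs per scenario), the chance of wrongly favouring the arm with more missing scores was 6% to 13% at 15% v 25%, and 12% to 38% at 10% v 30%. The nominal rate is 2.5%; at equal 20% loss it was 2.2%. For scale, the standard error of the difference is 15.35 × √(2/37) = 3.6 points.

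**5. How much of the loss could be death.** Role of transoral surgery cites 3-year overall survival of 86% and 84.5% in two surgical series not restricted to HPV-positive disease. At a constant hazard, deaths by 12 months are 1 − 0.86^(1/3) = 4.9% and 1 − 0.845^(1/3) = 5.5%. Deaths would then account for about a quarter of a 20% loss.

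**The case against.** The strongest opposing case has five parts.

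- **A single 12-month endpoint is legitimate.** It matches the aim of long-term swallowing function, and the 20% loss is budgeted correctly. This stands, and the proposed model keeps the same 12-month difference as its estimate.
- **Missing-data detail commonly sits in a full protocol or SAP, neither of which is shown.** This also stands, so the point does not rest on that silence. It rests on the test and covariates that the article does name; an SAP that followed them would leave the earlier scores out.
- **Recurrence does not remove a score.** Nothing in the article stops MDADI assessment at recurrence. A recurrent patient who attends at 12 months and swallows badly lowers the arm's mean. Only death necessarily removes a score.
- **The direction is open.** A reader might infer that the comparison favours the de-intensified arms, so that phase II could pass because of oncological failure. The documents do not support this. Toxicity-related loss in the control arms would bias the other way. Survival, disease-free survival and locoregional control are secondary outcomes, the monitoring committee reviews survival every 6 months, a stopping rule covers recurrence and death, and phase III tests overall survival.
- **A mixed model does not cure informative loss.** It assumes data are missing at random and implies scores after death. This is correct, and it is why a separate sensitivity analysis is needed. Scoring deaths as 20 merges survival into a swallowing measure, so it belongs beside the primary result and should not replace it.

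**Conclusion.** The point holds as an inexpensive gain in efficiency and robustness. The plan contains no arithmetic or power error here: 186 is right and preserves about 80% power at the back-solved SD of 15.35.

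The stated method leaves out MDADI scores that the trial collects. Using them would raise power to about 81% to 86% through repeated measures, or to about 84% to 90% through pre-surgery adjustment at a correlation of 0.3 to 0.5. A 10-point imbalance in missing scores, with missing patients 15 to 30 points worse, would shift the difference by 1.5 to 3.0 points. That is 15% to 30% of the target difference, and less than one standard error. The correlations, deficits and imbalances are all my assumptions.

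Two stronger readings should be avoided. The other MDADI visits are not wasted, since the functional panel is a secondary outcome. Nor does the article say that patients with recurrence leave the comparison.

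**What to change.** Within each randomisation, make the primary analysis a mixed model for repeated measures on MDADI at 4 weeks, 6 months and 12 months post-treatment. Include pre-surgery MDADI and the stratification variables as covariates, and take the 12-month arm difference as the primary estimate.

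Add one sensitivity analysis that assigns 20, the bottom of the scale in Table 3, to patients who die before 12 months and to those with recurrence and no 12-month score. Report it beside the primary result before the phase III decision.

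The cost is a change of wording, some programming and the added modelling assumptions. No new visits, data or patients are needed, and the sample size stays as stated.

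### The stated adjustment for the primary 12-month MDADI comparison leaves out the pre-surgery MDADI score and tumour subsite, forgoing precision that the collected data could supply

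*Protocol article*

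**What the plan says.** The phase II primary outcome is swallowing function, "measured using the 19-item composite MDADI score at 12 months post-treatment" (Protocol article, Primary outcome measures). Under Statistical analyses, arm means at 12 months are compared by a t-test or a nonparametric method, depending on the distributions. The article then says: "We will adjust for the randomisation stratification variables using regression techniques".

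Method of randomisation defines that set: "Participants will be stratified prior to randomisation by T stage, N stage, smoking history and treating centre".

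Two other places bear on the choice:

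- Assessments and outcomes lists MDADI first in its schedule: "The following assessments will be conducted prior to surgery, 4 weeks post surgery and at 4 weeks, 6, 12 and 24 months post treatment". A pre-randomisation measurement of the primary outcome therefore exists for each patient who completes it before surgery.
- Statistical analyses plans subgroup analyses of the swallowing endpoints by T stage and tumour subsite (tonsil, soft palate, tongue base), chosen "as the most likely relevant clinical co-variables affecting swallowing function". T stage is also in the adjustment set because it is a minimisation factor. Subsite appears only as a subgroup variable.

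**The concern.** For a continuous score measured before and after treatment, the baseline value of that score is the natural first covariate, and the stated set does not contain it. Subsite, one of the two swallowing co-variables that the article itself singles out, is also absent.

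The cost is in precision. Each randomisation is analysed separately with about 37 evaluable patients per arm. Minimisation balances T stage, N stage, smoking and centre, and does not directly control starting swallowing function. If baseline MDADI predicts the 12-month score, leaving it out makes the standard error larger than necessary and leaves chance baseline differences uncorrected in the estimate. The article states no SD. If the true SD is above the value implied by the sample size, the variance removed by a baseline covariate would help to protect the planned power.

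**Working it through.** **Inputs from the article (Sample size calculation, Phase II)**

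- Target difference of 10 points: "a 10-point difference in mean MDADI score can differentiate aspirators from non-aspirators".
- 80% power, two-sided 5% alpha.
- "a sample size of 148 patients is required", with 74 in each randomisation. Allocation is equal (19 per arm out of 38 at the interim), so 74/2 = 37 evaluable per arm.

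**Inputs not given, assumed here**

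- SD of 12-month MDADI: back-calculated from the sample size.
- Correlation r between pre-surgery and 12-month MDADI: 0.1 to 0.6. Strictly, this should be the partial correlation given the minimisation factors, since those are already adjusted for.
- R² for subsite: 0.02 to 0.10.

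**Step 1. Reproduce the plan's figure.** An unadjusted two-sample t-test with SD 15 and a difference of 10 needs 36.3 per arm. Rounded up this is 37, and 37 × 4 = 148, with power 80.8%. Solving the other way, 37 per arm at exactly 80% power implies an SD of 15.15. The 148 is thus consistent with a t-test that takes no credit for covariates.

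**Step 2. Add pre-surgery MDADI.** Residual SD = 15.15 × √(1 − r²). Power is recomputed for the t-test with 37 per arm. The approximate 95% CI half-width is 1.96 × residual SD × √(2/37). The last column, 15.15/√(1 − r²), is the largest unadjusted SD at which the adjusted analysis keeps 80% power.

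| Assumed r | Variance removed (r²) | Residual SD | Power | CI half-width | SD tolerated at 80% power |
|---|---|---|---|---|---|
| 0 | 0% | 15.15 | 80.0% | 6.9 | 15.1 |
| 0.1 | 1% | 15.07 | 80.4% | 6.9 | 15.2 |
| 0.2 | 4% | 14.84 | 81.6% | 6.8 | 15.5 |
| 0.3 | 9% | 14.45 | 83.6% | 6.6 | 15.9 |
| 0.4 | 16% | 13.88 | 86.4% | 6.3 | 16.5 |
| 0.5 | 25% | 13.12 | 89.9% | 6.0 | 17.5 |
| 0.6 | 36% | 12.12 | 93.8% | 5.5 | 18.9 |

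The one degree of freedom spent on baseline changes these powers by less than 0.02 percentage points.

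**Step 3. Chance imbalance.** If the baseline SD is also about 15 (assumption), the between-arm difference in mean baseline has standard error 15.15 × √(2/37) = 3.5 points, a 95% range of about ±6.9. At r = 0.5 with equal SDs, half of that, about ±3.5 points, carries into the unadjusted 12-month difference. The target difference is 10.

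**Step 4. Add subsite alone.** Three categories cost two degrees of freedom. With SD 15, the normal approximation and a penalty for those two degrees of freedom, power is 80.7% at R² = 0 and 81.5, 82.6 and 84.6% at R² = 0.02, 0.05 and 0.10. The gain is about 1 to 4 percentage points, at most a modest addition to baseline.

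**The case against.** The strongest reply is that nothing stated is wrong. Under randomisation the stated comparison is unbiased. Chance baseline imbalance is part of the sampling error that the standard error already covers, and 148 was sized for an unadjusted test. All of this stands. A reader might infer that the estimate is biased or that the trial is underpowered because baseline is left out. The article supports neither.

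A second reply is that a journal article summarises, that it does not say the adjustment is confined to these variables, and that an analysis plan not shown may add baseline. That is possible, so one cannot conclude that the final analysis will omit it. The article does name a set, however, and the point is about that set.

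Third, the size of the gain rests on a correlation that the article does not give, and there are reasons to expect a low value. Table 1 excludes patients with swallowing dysfunction before the index cancer, the scale is capped at 100, and surgery and adjuvant treatment lie between the two scores. This stands: at r = 0.1 or 0.2 the gain is 0.4 or 1.6 points of power.

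Finally, it is tempting to say that the article contradicts itself on subsite, or that it adjusts only for survival factors. Neither holds. Using subsite for subgroups is compatible with leaving it out of the main model, and T stage, the other named swallowing co-variable, is already adjusted for.

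**Conclusion.** The point holds as a recommendation for a better primary analysis. It does not show an error in the design. The stated set omits an already collected baseline of the primary outcome and one of the two swallowing co-variables that the article names. The analysis remains valid and the stated 80% power is unaffected.

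The gain from baseline ranges from almost nothing at r = 0.1 to about 10 points of power at r = 0.5 and 14 at r = 0.6. It rests on the implied SD of about 15.1, on 37 evaluable patients per arm, and on an assumed correlation that may lie at the low end. Subsite offers less. Even with a low correlation, including baseline costs almost nothing.

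**What to change.** Within each randomisation, prespecify one primary linear model (ANCOVA) of 12-month composite MDADI on arm, pre-surgery MDADI and the minimisation factors. Tumour subsite, in the three categories already used for the subgroup analysis, can be added as a secondary covariate with a smaller expected gain. Fix the model before outcome data are seen.

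Do not put the 4-week post-surgery MDADI in the primary model. The trial is open label and the article does not show that this questionnaire is completed before allocation, so the pre-surgery score is the safe baseline.

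The cost is one sentence, one degree of freedom for baseline and up to two more for subsite. No extra patients, visits or data are needed.
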